## 8.3 Study procedures

1. Patients will be recruited in two ways; 1. by means of posters hanging in the waiting room; patients can announce themselves to their treating therapist/physician or contact the researchers directly 2. Patients with a PD will be informed by the therapist/physician about the study. The therapist/physician informs the researchers, who will send information to the patient by mail and call the patients to invite them for an appointment. Interested patients will receive further information about the study during an appointment with one of the researchers. Furthermore, the researcher will check eligibility for inclusion. At the end of the appointment patients will be given informed consent forms. The patients are allowed to take the time they need to make a decision about participation. Patients who decide to participate will be asked to sign informed consent.
2. Diagnostic instruments before inclusion: a. Any PD diagnosis will be confirmed using the SCID-5-PD
3. Informed consent: During an intake interview with the researchers, patients are informed about the study verbally and formally. If the patient had enough time to consider whether he/she wants to participate into this study, the patient is asked to give written, informed consent.
4. Randomization: After patients are included and have given informed consent, patients are randomized into one of the two conditions.
5. Questionnaires will be administered at baseline (before randomization), after weeks (post EMDR) and three, six and twelve months after onset of the study.
6. Interview: all participants in the EMDR group will be requested to participate in a qualitative interview about their experiences with EMDR therapy.
7. Patients in the experimental group are treated with ten biweekly, ninety minute, EMDR sessions. These patients are compared with a waiting list condition. After three months of follow-up patients can decide whether they want to have standard treatment for PD.

#### **8.4 Withdrawal of individual subjects**

Subjects can leave the study at any time for any reason if they wish to do so without any consequences. The investigator can decide to withdraw a subject from the study for urgent medical reasons.

##### **8.4.1 Specific criteria for withdrawal (if applicable)**

#### **8.5 Replacement of individual subjects after withdrawal**

Inclusion is continued until 159 participants have been included. We attempt to collect reasons for withdrawal. However, patients are not obliged to give a reason.

#### **8.6 Follow-up of subjects withdrawn from treatment**

Patients will be asked to continue the assessments if they prematurely stop the treatment sessions. It is attempted to collect reasons for withdrawal. However, patients are not obliged to give a reason for withdrawal and withdrawal of assessment.

#### **8.7 Premature termination of the study**

Aside from individual withdrawal, we expect no event that will lead to premature termination of the study. However, if this study will end prematurely, this will have no influence on the treatment of patients for their PD.

## 9. SAFETY REPORTING

### 9.1 Temporary halt for reasons of subject safety

In accordance to section 10, subsection 4, of the WMO, the sponsor will suspend the study if there is sufficient ground that continuation of the study will jeopardize subject health or safety. The sponsor will notify the accredited METC without undue delay of a temporary halt including the reason for such an action. The study will be suspended pending a further positive decision by the accredited METC. The investigator will take care that all subjects are kept informed.

### 9.2 AEs, SAEs and SUSARs

#### 9.2.1 Adverse events (AEs)

Adverse events are defined as any undesirable experience occurring to a subject during the study, whether or not considered related to [the investigational product / trial procedure/ the experimental intervention]. All adverse events reported spontaneously by the subject or observed by the investigator or his staff will be recorded.

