### **3. STUDY DESIGN**

To assess the surplus value of EMDR compared to waiting list, a single-blind RCT with two groups (EMDR versus waiting list) will be performed. The experimental group will receive ten bi-weekly EMDR sessions of ninety minutes each (with a total duration of 5 weeks). Data will be collected at baseline, 5 weeks (post EMDR-treatment) and three-, six- and twelve-months after onset of the study.

Based on a feasibility analysis, inclusion of patients will take 1 year.

The study will be conducted at Parnassia Psychiatric Institute and GGZ Delfland.

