## **5. TREATMENT OF SUBJECTS**

### **5.1 Investigational product/treatment**

Control condition: Participants in the waiting list condition will be seen once by a study therapist and informed about the course of the study. After three months patients will be offered the opportunity of following a standard treatment for their PD. This period is shorter than the regular waiting time for treatment of PD, which ranges 6 to 12 months.

Experimental condition: The Dutch version of the standard EMDR protocol (de Jongh & ten Broeke, 2019) will be used. The protocol will focus on the most distressing target memory. A total of 10 biweekly sessions of EMDR will be applied with a duration of 90 minutes per session. EMDR therapists are psychologists who have followed at least the basic EMDR training certified according to the guidelines of EMDR Europe. Group supervisions will be provided monthly by consultants in the treatment of EMDR. Additional supervision by telephone or e-mail is available on request. The treatment sessions will be videotaped; 10% will be randomly selected and rated by trained and blinded raters for therapist competence and treatment protocol adherence.

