#### **9.5 [Data Safety Monitoring Board (DSMB) / Safety Committee]**

EMDR is an evidence-based treatment for PTSD and is found to be safe. A DSMB is therefore not instituted.

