### 11.4 Benefits and risks assessment, group relatedness

Patients with PD suffer from low self-esteem, have severe impairments in the regulation of emotions and interpersonal functioning and their quality of life is low. In a recent study, EMDR reduced BPD symptoms (De Jongh et al. 2020). In another study, psychological symptoms, psychological functioning, and personality functioning were positively affected by 5 EMDR sessions in all PDs (Hafkemeijer et al., submitted for publication). Thus, it is expected that patients who receive EMDR, will experience a reduction in PD symptoms and an improvement in psychological and personality functioning. In addition, EMDR is safe and not associated with an increase of self-injurious behaviour, suicidal gestures, suicides or hospital admissions. is applied in addition to treatment as usual for PD with regular meetings. In case emotions or traumatic intrusions increase in the two or three days after a session of EMDR, patients have the opportunity to discuss their symptoms with the EMDR- and PD-therapists. Also, no risks are expected due to the data collection.

The study requires participants in the control group to not receive treatment for three months. If necessary or if the participant no longer wants to participate, he or she is free to terminate participation.

With participation into this study, patients contribute to knowledge about treatment and can therefore contribute to the quality of treatment.

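### Adverse events are recorded only if volunteered or observed, while contact with study staff differs sharply by arm, so they are not ascertained equally and events in untreated controls can be missed

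*Protocol*

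**What the plan says.** **Capture rule.** Protocol section 9.2.1: "All adverse events reported spontaneously by the subject or observed by the investigator or his staff will be recorded". The rule is not confined to a time window within the study. Section 8.3 schedules questionnaires in both arms, but no adverse-event question is among the listed measures or procedures.

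**Contact in the EMDR arm.** Section 3: "The experimental group will receive ten bi-weekly EMDR sessions of ninety minutes each (with a total duration of 5 weeks". Section 8.3 adds a qualitative interview for EMDR participants only. Items 4 and 5 of its guide (Appendix A) ask about disadvantages of the treatment and about side effects shortly after a session. Section 11.4 also describes an opportunity to discuss symptoms that increase in the days after a session.

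**Contact in the waiting-list arm.** Section 5.1: "Participants in the waiting list condition will be seen once by a study therapist and informed about the course of the study". Section 11.4: "The study requires participants in the control group to not receive treatment for three months".

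**Contact common to both arms.** Section 3 sets five assessments: baseline, 5 weeks, and 3, 6 and 12 months. The TiC-P (sections 8.1.2 and 10.2) collects use of medical services for the economic evaluation. It is not named as a source of adverse events.

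**Use of the data.** Adverse events are not a listed endpoint in section 8.1, and section 10 describes no between-arm comparison of them.

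**The concern.** With passive capture, the chance that an event is recorded grows with the number of occasions on which it can be mentioned or seen. The design gives one arm many more such occasions, concentrated in the first five weeks. Two things follow.

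- If true event rates were equal, the recorded data would tend to show more events under EMDR.
- An event in a control patient during the untreated three months can go unrecorded unless the patient raises it or staff notice it. Under section 9.2.2, reporting of a serious event starts once the investigator knows of it, so missed capture also means missed reporting.

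What is at stake is safety oversight during the trial and the fairness of any safety statement made from it. This is a rule that the protocol itself states, not a detail left to an analysis plan.

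**Working it through.** The protocol gives no figure for adverse-event capture, so there is none to reproduce. The check counts contacts and then shows what unequal counts could do.

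**1. Scheduled contacts** (sections 3 and 5.1)

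| | EMDR | Waiting list | Ratio |
|---|---|---|---|
| Study therapist only | 10 | 1 | 10 |
| Plus assessments to month 3 (baseline, week 5, month 3) | 10 + 3 = 13 | 1 + 3 = 4 | 3.25 |
| Plus all five assessments | 10 + 5 = 15 | 1 + 5 = 6 | 2.5 |

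The EMDR interview is not counted and would widen the gap. The shared visits reduce the imbalance but do not remove it.

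**2. Illustration.** These are assumptions, not figures from the protocol: equal true event rates in weeks 0-5, a chance *p* of 0.1, 0.2 or 0.3 that an event is captured at any one later contact, and independent contacts. The event is equally likely to fall with *k* = 0, 1, ..., 10 sessions still to come. Let *m* be the number of post-baseline assessments counted (2 to month 3, 4 to month 12). The single waiting-list therapist contact is taken to precede the event.

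- Waiting list: 1 − (1 − p)^m
- EMDR: 1 − (1 − p)^m × g, where g is the mean of (1 − p)^k over k = 0 to 10, that is [1 − (1 − p)^11] / (11p)

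g = 0.624, 0.416 and 0.297 for p = 0.1, 0.2 and 0.3.

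Worked case, p = 0.1 and m = 2: the waiting list gives 1 − 0.81 = 0.19; EMDR gives 1 − 0.81 × 0.624 = 0.495; the ratio is 0.495 / 0.19 = 2.6.

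| p | To month 3 (m = 2): EMDR vs control | Ratio | To month 12 (m = 4): EMDR vs control | Ratio |
|---|---|---|---|---|
| 0.1 | 49% vs 19% | 2.6 | 59% vs 34% | 1.7 |
| 0.2 | 73% vs 36% | 2.0 | 83% vs 59% | 1.4 |
| 0.3 | 85% vs 51% | 1.7 | 93% vs 76% | 1.2 |

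**3. Sensitivity to the model**

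- If the single waiting-list contact comes after the event, control capture becomes 1 − (1 − p)^(m+1). To month 3 that is 27%, 49% and 66%, and the ratios fall to 1.8, 1.5 and 1.3. To month 12 it is 41%, 67% and 83%, with ratios of 1.4, 1.2 and 1.1.
- A cruder model gives every event all 12 (EMDR) or 3 (control) post-baseline contacts to month 3. The ratio is [1 − (1 − q)^12] / [1 − (1 − q)^3]: 0.718 / 0.271 = 2.65 at q = 0.1, and 1.000 / 0.875 = 1.14 at q = 0.5.

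The size depends heavily on the assumed capture chance. The direction does not change.

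**4. Effect of asking both arms the same question** at week 5 and month 3. Take a sensitivity *s* of 0.80 to 0.95 per visit and spontaneous capture *q* of 0.1 to 0.3 at the other contacts. The ratio is [1 − (1 − s)²(1 − q)^10] / [1 − (1 − s)²(1 − q)]. At s = 0.80 and q = 0.3 it is 0.999 / 0.972 = 1.03; at s = 0.95 and q = 0.1 it is 0.999 / 0.998 = 1.00.

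**The case against.** **No planned analysis uses these data.** This stands. Section 10 contains no between-arm adverse-event comparison, and the primary analysis, sample size and economic evaluation are untouched. The harm is confined to oversight and to any later safety statement.

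**Controls are not invisible.** This stands in part. Symptom worsening is measured on the same schedule in both arms (sections 8.1 and 8.3), and the TiC-P may reveal health-care use after an event. A reader might infer that the arms' safety data cannot be compared at all, or that deterioration in controls goes unseen; the protocol supports neither. But none of these instruments is named as an adverse-event source.

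**The bias could be overstated.** Crediting controls with the week-5 visit alone (m = 1) gives ratios of 0.439 / 0.10 = 4.4 down to 0.792 / 0.30 = 2.6. A reader might take that as the size of the problem. It ignores the common visits at 3, 6 and 12 months, at which section 9.2.1 still allows events to be recorded. A single low capture chance is also unlikely to suit every event type; nothing in the protocol supports 10-30% for an admission or a suicide attempt.

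**Two statements look damaging but do not bear on this point.** Section 11.4 says that EMDR is "not associated with an increase of self-injurious behaviour, suicidal gestures, suicides or hospital admissions". That is a benefit-risk expectation written before the trial, not a conclusion from its data. Section 9.5 says "A DSMB is therefore not instituted". The absence of a board does not determine whether events are ascertained equally.

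**The contact count is not fully settled.** This stands. Section 11.4 describes the treatment as given on top of usual care for personality disorder with regular meetings, and also says that controls go three months without treatment.

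**An added enquiry could unblind assessors.** This stands. Under section 8.2 the data collectors are kept unaware of allocation, and the CAPS-5, listed in section 8.1.1 as a main endpoint, is clinician-administered. An open question put by the same person before rating invites talk of EMDR sessions. The remedy has to be built around this.

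**Conclusion.** The point holds as one of unequal ascertainment. Following the protocol as written, an adverse event has more chances to be recorded in the EMDR arm, and some events in controls untreated for three months can be missed. The contact count is 13 against 4 to month 3 and 15 against 6 to month 12.

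The size of the resulting bias cannot be derived from the protocol. Under equal true rates and an assumed 10-30% capture chance per contact, the apparent ratio is about 2.6 to 1.7 to month 3 and about 1.7 to 1.2 to month 12. It is smaller still if the one waiting-list contact comes late or if capture per contact is higher. These ratios indicate direction and plausible scale only.

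This merits a change because the remedy is cheap and improves oversight of an untreated group. It is not a threat to the primary efficacy result.

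**What to change.** In section 9.2.1, add the following.

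- At each scheduled post-baseline assessment (5 weeks, and 3, 6 and 12 months), participants in both arms receive the same adverse-event enquiry: one open question, plus fixed items on self-harm, suicide attempt and hospital admission since the last assessment.
- The enquiry is a self-completed form, or is asked only after all blinded outcome ratings at that visit are finished. The answers are kept from the blinded raters.
- Any between-arm safety summary is based on these answers. Events known only from EMDR sessions or the EMDR interview are still recorded, but are listed separately.

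Also reconcile the two statements in section 11.4 on treatment as usual and on untreated controls, and state which contacts each arm has.

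**Cost.** A few minutes at each existing visit and one case report form page; no new visits. More events will be recorded, with the related paperwork. A small risk of unblinding remains, which the ordering above controls. Participants know their allocation, so some difference in willingness to report may persist.

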#### 9.2.2 Serious adverse events (SAEs)

A serious adverse event is any untoward medical occurrence or effect that

- results in death;
- is life threatening (at the time of the event);
- requires hospitalization or prolongation of existing inpatients' hospitalization;
- results in persistent or significant disability or incapacity;
- is a congenital anomaly or birth defect; or
- any other important medical event that did not result in any of the outcomes listed above due to medical or surgical intervention but could have been based upon appropriate judgement by the investigator.

An elective hospital admission will not be considered as a serious adverse event.

*< Please describe the procedures for handling the serious adverse events. If certain SAEs do not require immediate reporting by the investigator to the sponsor, please specify.>*

The investigator will report all SAEs to the sponsor without undue delay after obtaining knowledge of the events, except for the following SAEs: *<specify which*

*SAEs do not require immediate reporting by the investigator to the sponsor, if applicable> .*

The sponsor will report the SAEs through the web portal *ToetsingOnline* to the accredited METC that approved the protocol, within 7 days of first knowledge for SAEs that result in death or are life threatening followed by a period of maximum of 8 days to complete the initial preliminary report. All other SAEs will be reported within a period of maximum 15 days after the sponsor has first knowledge of the serious adverse events.

*< If certain SAEs do not require( expedited) reporting to the accredited METC, please specify these SAEs as well as the frequency of reporting of these SAEs in line listings, or in a annual safety report or otherwise.>*

### **9.2.3 Suspected unexpected serious adverse reactions (SUSARs)**

*<This chapter is only applicable for studies with an investigational medicinal product>*

Adverse reactions are all untoward and unintended responses to an investigational product related to any dose administered.

Unexpected adverse reactions are SUSARs if the following three conditions are met:

1. the event must be serious (see chapter 9.2.2);
2. there must be a certain degree of probability that the event is a harmful and an undesirable reaction to the medicinal product under investigation, regardless of the administered dose;
3. the adverse reaction must be unexpected, that is to say, the nature and severity of the adverse reaction are not in agreement with the product information as recorded in:
  - Summary of Product Characteristics (SPC) for an authorised medicinal product;
  - Investigator's Brochure for an unauthorised medicinal product.

The sponsor will report expedited the following SUSARs through the web portal *ToetsingOnline* to the METC *<reporting via webportalToetsingOnline is only applicable for investigator initiated studies>*:

- SUSARs that have arisen in the clinical trial that was assessed by the METC;

- SUSARs that have arisen in other clinical trials of the same sponsor and with the same medicinal product, and that could have consequences for the safety of the subjects involved in the clinical trial that was assessed by the METC.

The remaining SUSARs are recorded in an overview list (line-listing) that will be submitted once every half year to the METC. This line-listing provides an overview of all SUSARs from the study medicine, accompanied by a brief report highlighting the main points of concern.

The expedited reporting of SUSARs through the web portal Eudravigilance or ToetsingOnline is sufficient as notification to the competent authority.

The sponsor will report expedited all SUSARs to the competent authorities in other Member States, according to the requirements of the Member States.

The expedited reporting will occur not later than 15 days after the sponsor has first knowledge of the adverse reactions. For fatal or life threatening cases the term will be maximal 7 days for a preliminary report with another 8 days for completion of the report.

### **9.3 Annual safety report**

In addition to the expedited reporting of SUSARs, the sponsor will submit, once a year throughout the clinical trial, a safety report to the accredited METC, competent authority, and competent authorities of the concerned Member States.

This safety report consists of:

- a list of all suspected (unexpected or expected) serious adverse reactions, along with an aggregated summary table of all reported serious adverse reactions, ordered by organ system, per study;
- a report concerning the safety of the subjects, consisting of a complete safety analysis and an evaluation of the balance between the efficacy and the harmfulness of the medicine under investigation.

### **9.4 Follow-up of adverse events**

All AEs will be followed until they have abated, or until a stable situation has been reached. Depending on the event, follow up may require additional tests or medical procedures as indicated, and/or referral to the general physician or a medical specialist.

SAEs need to be reported till end of study within the Netherlands, as defined in the protocol

#### **9.5 [Data Safety Monitoring Board (DSMB) / Safety Committee]**

EMDR is an evidence-based treatment for PTSD and is found to be safe. A DSMB is therefore not instituted.

## 10. STATISTICAL ANALYSIS

Most data are quantitative and will be analyzed using SPSS 25 (SPSS Inc., Chicago, IL). The aim is to collect complete data. It is attempted to avoid missing data. In case that missing data occurs, patients with missing data will not be excluded, since multiple measurement points are used.

### 10.1 Primary study parameter(s)

The primary study parameter is the number of diagnosed PD symptoms, over five moments of measurement. In order to test the effectiveness of EMDR in reducing the number of PD symptoms over time, a linear mixed model (LMM) with intention-to-treat will be used. Within-subjects factor 'Time' has five levels (baseline vs. post-intervention vs. three-month vs. six-month vs. twelve-month follow-ups) and between-subjects factor 'Group' has two (EMDR vs. waiting list). Corrected post-hoc analyses will be performed where significant effects are found.

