## 2. OBJECTIVES

### *Primary Objectives:*

- 1) How effective is EMDR therapy compared to waiting list on symptoms of PD?
- 2) How cost-effective is EMDR therapy versus a wait-list control condition?

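### The primary model runs to 12 months under a waiting-list label that holds for only three, and it names no primary contrast

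*Protocol*

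**What the plan says.** - **Question.** Section 2 gives as the first primary objective: "How effective is EMDR therapy compared to waiting list on symptoms of PD". The second is: "How cost-effective is EMDR therapy versus a wait-list control condition".
- **Primary analysis (10.1).** "The primary study parameter is the number of diagnosed PD symptoms, over five moments of measurement". The model is a linear mixed model by intention to treat. Its time factor reads "Within-subjects factor 'Time' has five levels (baseline vs. post-intervention vs. three-month vs. six-month vs. twelve-month follow-ups", and its other factor reads "between-subjects factor 'Group' has two (EMDR vs. waiting list". The comparator therefore carries one label at all five times.
- **Visit contrasts (10.1).** "Corrected post-hoc analyses will be performed where significant effects are found". No visit or contrast is named as primary.
- **Control condition.** Section 5.1: "After three months patients will be offered the opportunity of following a standard treatment for their PD". The Summary and 11.4 both put the period without treatment at three months. Section 8.3, item 7, says "After three months of follow-up patients can decide whether they want to have standard treatment for PD" and does not say whether this covers one arm or both.
- **Sample size (4.4).** 132 patients, from five repeated measurements, a correlation of 0.7 and one effect size of 0.43, then 159 to allow for dropout.

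Beyond intention to treat, nothing says how standard treatment started after month 3 is to be handled or described.

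**The concern.** Two of the four post-baseline visits fall after the waiting-list condition has ended, yet they enter the primary test as if it continued. At 5 weeks and 3 months the contrast is EMDR against no treatment. At 6 and 12 months it is EMDR first against delayed access to standard treatment. Both are legitimate randomised comparisons, but only the first answers Objective 1.

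Because no contrast is designated, the result that decides the trial could be a Group effect averaged over both comparisons, a Time by Group interaction driven by what happens after month 3, or a visit contrast picked once an omnibus effect is significant. An averaged effect shrinks if the arms converge late. An interaction can be significant for a reason that has nothing to do with benefit over waiting list.

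Objective 2 has the same difficulty. Section 10.2 states no time horizon. If the economic analysis uses all 12 months of data collection, 12 − 3 = 9 of those months follow the waiting-list period. Section 5.1 adds that the offer comes sooner than the regular wait of 6 to 12 months, so later control costs need not reflect either a waiting list or usual access.

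**Working it through.** **Inputs.** From 4.4: 132 patients, correlation ρ = 0.7, effect d = 0.43, α = 0.05, power 0.80. Assumed, because not stated: equal arms (66 each), a two-sided test, the same correlation between all pairs of visits, and no difference at baseline. The effect at 6 and 12 months is not given, so it is varied from 0 to 0.43.

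**1. The plan's own figure.** The formula for k equally correlated measurements is n per arm = 2(1.960 + 0.842)² × [1 + (k − 1)ρ]/k ÷ d². With k = 5 the variance factor is (1 + 4 × 0.7)/5 = 0.76 and n = 64.5, so 65 per arm or 130 in total. Using the t distribution, 66 per arm gives power 0.803, which is the stated 132. With k = 4 the formula also gives 132; with k = 3 (visits to 3 months only) it gives 136. The stated size thus counts the late visits as carrying the same effect of 0.43.

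**2. Group effect averaged over the four post-baseline visits, no baseline adjustment.** Variance factor (1 + 3 × 0.7)/4 = 0.775; SE = √(2 × 0.775/66) = 0.153. Average effect = (2 × 0.43 + 2 × late effect)/4.

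| Late effect | Average | Average/SE | Power |
|---|---|---|---|
| 0.43 | 0.430 | 2.81 | 80% |
| 0.30 | 0.365 | 2.38 | 66% |
| 0 | 0.215 | 1.40 | 29% |

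**3. Time by Group test (4 df).** Non-centrality λ = (66/2) × Σ(difference at each visit − mean difference)² ÷ (1 − 0.7), taken over all five visits.

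| Differences, baseline to 12 months | Sum of squares | λ | Chance of significance |
|---|---|---|---|
| 0, 0.43, 0.43, 0.43, 0.43 | 0.1479 | 16.3 | 91% |
| 0, 0.43, 0.43, 0.30, 0.30 | 0.1235 | 13.6 | 85% |
| 0, 0.43, 0.43, 0, 0 | 0.2219 | 24.4 | 99% |
| 0, 0, 0, −0.30, −0.30 | 0.1080 | 11.9 | 79% |

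In the last row EMDR has no effect through 3 months and controls then move ahead by 0.30. The omnibus test still succeeds about four times in five.

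**4. One contrast at 3 months, 66 per arm.**
- No baseline adjustment: SE = √(2/66) = 0.174; 0.43/0.174 = 2.47; power about 69%.
- Baseline adjusted, correlation 0.7: SE = √(2 × (1 − 0.49)/66) = 0.124; ratio 3.46; power about 93%.
- Baseline adjusted, correlation 0.5: SE = √(2 × (1 − 0.25)/66) = 0.151; ratio 2.85; power about 81%.

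**The case against.** The best defence is that the later visits have a purpose. Section 1 wants effects on loss of diagnosis and costs at one year, and an intention-to-treat comparison at 12 months is a valid comparison of randomised strategies. Time is categorical, so the 5-week and 3-month contrasts can already be estimated from the planned model. This stands. It reduces the fault to a missing hierarchy and a wrong label, but it does not supply a designated test.

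Three stronger readings are tempting, and the protocol does not support them.

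- *By 6 and 12 months the controls are a treated group.* Treatment is offered, not required; uptake is not given; and 8.3 does not confine the offer to controls. The late comparator is an unknown mixture.
- *Running to 12 months ruins the power.* One could set a Group effect averaged over all five levels (about 20% to 48% power for late effects of 0 to 0.3) against 93% for a 3-month contrast. That is not like with like. The first averages in baseline and is unadjusted, and has only about 61% power even with 0.43 at every later visit. The second is baseline-adjusted, and falls to 69% without adjustment. With the same adjustment, the average of the four post-baseline visits has about 97% power at a late effect of 0.3, more than the 3-month contrast, and about 63% at 0.
- *An effective treatment will be declared ineffective.* On the usual Time by Group reading, power stays at about 85% to 99%. The weakness there is what a significant result means.

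**Conclusion.** The point holds as one of hierarchy and labelling, and it should be fixed. The primary question concerns an untreated comparator that exists for three months, while the primary model spans twelve under that label and designates no contrast. How much this matters depends on which term is taken as decisive. An averaged post-baseline Group effect loses between 14 points of power (80% to 66%, late effect 0.3) and 51 points (80% to 29%, late effect 0). The interaction loses little power, but can be significant with no benefit over waiting list, about 79% of the time in the case shown. These figures rest on 132 analysed patients in equal arms, a correlation of 0.7 throughout, and assumed late effects. The protocol offers no basis for choosing among those effects.

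**What to change.** - **10.1:** name one primary contrast inside the waiting-list period, not conditional on any omnibus result. An example is EMDR minus waiting list in ADP-IV symptom count at 3 months, from the same mixed model with baseline adjusted for or constrained equal. The 5-week visit, or both visits together, would also be defensible; what matters is fixing the choice beforehand. The Summary and 8.1.1 also list CAPS-5 as a main outcome, and the wording should say how it relates to this test.
- **10.1:** make the 6- and 12-month contrasts secondary and call them a comparison of EMDR first with delayed access to standard treatment. Describe treatment received in both arms from the TiC-P.
- **4.4:** restate the basis of 132 for the named contrast, with the assumed baseline-to-3-month correlation. Without baseline adjustment, the 3-month contrast would need 170 patients before dropout for 80% power.
- **10.2:** report the economic result to 3 months as the waiting-list comparison, and label the 12-month result as the strategy comparison. The one-year aim is kept under its proper name.
- **5.1, 8.3 and 11.4:** reconcile who is offered standard treatment and when. Section 11.4 also contains an incomplete sentence about something given alongside usual PD treatment, which sits badly with a no-treatment comparison.

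The cost is wording. No new data are needed, and no extra patients if the contrast is baseline-adjusted and the correlation is near the assumed value. The 12-month result becomes secondary.
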